### Enrolment

- 1) Patients newly diagnosed to have or with known history of type 2 diabetes attending the clinic who fulfil the inclusion and have no exclusion criteria will be invited to participate and explained the nature of the AP-JD Program.
- 2) Patients will be asked to provide written informed consent and give permission to the care team to ascertain clinical status by telephone or email as well as obtain their clinical and biochemical data for analysis and research purpose at least on a yearly basis for 3 years.

### Comprehensive assessment

- 1) The following information will be collected from all patients:
  - a) Personal history on occupation, education, smoking and alcohol drinking.
  - b) Family history on diabetes and other illnesses.
  - c) History of diabetes-related complications, illnesses and symptoms.
  - d) Information on diabetes education and self-care.
  - e) History of cancers and other medical conditions.
  - f) Major clinical events and hospitalizations
  - g) Medications
- 2) Blood pressure and anthropometric measurements including body weight and height, waist and hip circumferences.
- 3) All patients will attend the CA session after at least 8 hours of fasting for measurement of plasma glucose (PG) and lipids (total cholesterol, triglyceride, HDL-C and LDL-C);

HbA1c; renal/liver function test; estimated glomerular filtration rate (eGFR) and complete blood count. A random spot urine will be collected for measurement of albumin-creatinine ratio (ACR). If fasting is not possible, TC and HDL-C are acceptable for lipid profile.

- 4) The doctor will perform eye (ophthalmoscopy through dilated pupils) and feet examination (reflexes, foot pulses and sensation) or arrange these to be performed by appropriate care professionals.
- 5) Alternatively, the nurse can be taught to use doppler scan, monofilament and graduated tuning fork to examine the feet.
- 6) He/she can also be taught how to use fundus camera (if available) to take retinal pictures which will be reviewed by the doctor.
- 7) The patient will complete the following questionnaires to assess psychological well being and compliance:
  - a) Quality of life using ED-5Q (patients' mobility, self-care, usual activities, pain/discomfort and anxiety/depression)
  - b) 4-item compliance questionnaire (CQ4)
  - c) Depression questionnaire (PHQ9)
- 8) Depending on the interests of the investigators, there are additional questionnaires which can be used to assess self efficacy, diabetes related distress, personal habits, psychological mood and health perception which can help the care team to provide education and empowerment (see appendix).
- 9) All patients will undergo repeat CA and complete these questionnaires at 12 and 24 months.
- 10) Due to the busy nature of the clinic, the nurse and doctor will first enter data using the CA and FU CRFs followed by data entry into the portal.
- 11) At baseline, year 1 and 2 as well as close out of study, all outcome measures and medications will be ascertained by phone or face to face interview (CRF: 1-5).

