#### Objectives and expected outcomes of AP -JD Program

In this demonstration project (Asia Pacific JADE and DIAMOND Program, AP-JD in short) supported by ADF, patients will be recruited from different sites across Asia, with each site recruiting at least 600 type 2 diabetic patients. After explanation by trained doctors and nurses, and with written informed consent, patients will be randomized to either the JADE (n=300, structured care) or DIAMOND (n=300, usual care) group. All patients will undergo a comprehensive assessment (CA) at baseline and yearly thereafter. Patients in the JADE group will be further managed by a doctor-nurse-HCA team according to a protocol based on risk stratification with predefined follow up (FU) schedules together with shared information and decision support (i.e. structured collaborative care). The DIAMOND protocol involves only baseline and yearly CA without predefined FU schedules or feedback of information between CA visits (i.e. usual care). The primary composite endpoint is all-diabetes related clinical endpoints. The secondary composite endpoint is attainment of treatment goals and/or control of risk factors. The tertiary changes are behavioral changes, psychological well being and quality of life.

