## **SETTING AND PATIENTS**

In this program, 600 consecutive type 2 diabetic patients will be recruited from each participating centre during a 6-8 month period, with randomization to either the JADE or DIAMOND group in a 1:1 ratio.

*Inclusion criteria*

- 1) Type 2 diabetic patients who are willing or can be persuaded to return for 'regular' follow-up at 3-4 monthly intervals
- 2) Aged  $\geq 18$  years
- 3) Patients with newly diagnosed or established disease, treated with lifestyle modification or blood glucose lowering drugs including oral agents with or without insulin
- 4) For newly diagnosed type 2 diabetic patients, their plasma glucose levels should be:
  - a) Fasting plasma glucose (PG)  $\geq 7.0$  mmol/L on 2 or more occasions, and/or
  - b) Random or 2-hour PG  $\geq 11.1$  mmol/L (after 75 gram oral glucose tolerance test) on 2 or more occasions, and/or
  - c) HbA1c  $\geq 6.5\%$

*Exclusion criteria*

- 1) Type 1 diabetes defined as a history of ketosis at diagnosis [acute symptoms with heavy ketonuria ( $>3+$ ) or ketoacidosis] or continuous requirement of insulin within one year of diagnosis (38).
- 2) Patients with reduced life expectancy (e.g. less than 6 months) due to recent diagnosis of advanced cancers (e.g. within last 2 years) and other life-threatening conditions.
- 3) Patients with a mental condition rendering them unable to understand the nature, scope, and possible consequences of the study.
- 4) Patients actively enrolled in another intervention study.
- 5) Patients who are unwilling to return for regular follow up.

**OUTCOME MEASURES***Composite primary endpoint (CRF (1-5))*

- 1) Incidence of all diabetes-related endpoints including:
  - a) cardiovascular events (acute myocardial infarction, revascularisation procedures, heart failure, unstable angina, arrhythmia, stroke, transient ischemic attacks requiring hospital admissions) and related death
  - b) chronic kidney disease (eGFR  $< 60$  ml/min/1.73m^2) or end stage renal disease (dialysis and/or eGFR  $< 15$  ml/min/1.73m^2) and related death
  - c) visual impairment (corrected visual acuity of 20/200 or worse) or eye surgery (cataract removal, retinal surgery and vitrectomy)

- d) lower extremity amputation or foot ulcers requiring hospitalizations
- e) major infections – pulmonary and non-pulmonary requiring hospitalizations
- f) all-site cancers
- g) death

Composite secondary endpoint

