#### Logistics and timeline

The following diagram summarises the flow of the study including approval of local institutional board, staff recruitment and training, use of portal and patient enrolment. We expect completion of recruitment within 6-8 months after all logistics are put in place. All patients will be followed up for at least 24 months with completion of follow up of all randomized patients, 3 years after the first patient is entered the study.

[figure not shown]

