## **DATA ANALYSIS**

All data will be analyzed using the SPSS statistical software (Windows 13.0 version, Chicago, USA). A p value of 0.05 or less (2-tailed) will be considered significant. For the primary composite endpoint, an intention to treat analysis will be performed including all patients randomized to both groups who have at least returned for one visit or contacted by phone once post randomization to ascertain clinical status (alive, dead or hospitalized). Descriptive analysis will be used to report all clinical and laboratory parameters. Student's t-test, Chi-squared test and Analysis of Co-variance will be used for between-group and within-group comparisons for all baseline data and endpoints, as appropriate. Kaplan-Meier curve analysis will be used to compare the incidence of primary composite endpoint between the JADE and DIAMOND group adjusted for age, sex, ethnicity and disease duration. Interaction between group assignment and covariates including age, gender, duration of diabetes (< or ≥8 years), socioeconomic group, complications, risk factors, JADE risk categories, compliance and psychological health parameters will be examined. Logistic regression will be used to determine independent predictors for achieving primary composite endpoint using all relevant covariates including age, gender, duration of diabetes (< or ≥8 years), centre characteristics, socioeconomic group, risk levels, metabolic and risk factor control, compliance, self care, psychological health parameters and intervention groups.

A per protocol analysis will be performed in the JADE group with details of intervention, where we shall compare baseline clinical profile, care processes, number of visits and use of medications between patients who develop and those who do not develop clinical endpoints. A sensitivity analysis will also be performed using hazard rates of the JADE and DIAMOND group amongst those who have defaulted.

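### Phone or interview is an allowed route for every primary outcome, but the eGFR and visual-acuity components need a measurement that is scheduled in both arms only up to month 24

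*Protocol*

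**What the plan says.** - **Route.** Protocol, Comprehensive assessment, item 11: at baseline, years 1 and 2 and close-out, "all outcome measures and medications will be ascertained by phone or face to face interview (CRF: 1-5"). The same form numbers head the primary composite under Outcome Measures.
- **Components defined by a measurement.** Outcome Measures lists "visual impairment (corrected visual acuity of 20/200 or worse"), chronic kidney disease as an eGFR below 60, and "end stage renal disease (dialysis and/or eGFR" below 15).
- **Where they are measured.** The CA laboratory list includes "renal/liver function test; estimated glomerular filtration rate (eGFR) and complete blood count". Study Design has the nurse measure visual acuity at the CA. Timing: "All patients will undergo repeat CA and complete these questionnaires at 12 and 24 months".
- **Length of follow-up.** Logistics and timeline: "All patients will be followed up for at least 24 months with completion of follow up of all randomized patients, 3 years after" [entry of the first patient]. Study Design gives a total of 2.5 to 3 years.
- **Who is analysed.** Data Analysis takes into the primary analysis randomised patients "who have at least returned for one visit or contacted by phone once post randomization to ascertain clinical status (alive, dead or hospitalized"). Default and Missing Data foresees at least yearly remote contact for patients who cannot come back for a CA.
- **Contact between CAs.** In JADE, tests ordered by the doctor, renal function among them, are to be ready before each follow-up visit (Intervention – JADE Group, item 6). DIAMOND runs "without predefined FU schedules or feedback of information between CA visits" (Executive Summary).

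**The concern.** An interview can pick up a death, an admission, an operation, dialysis, an amputation or a cancer diagnosis. It cannot show that eGFR is below 60 or that corrected acuity is 20/200 or worse. For those components, item 11 names a route that cannot deliver the outcome.

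Two consequences matter for the primary comparison. First, a patient without a CA can be in the analysis with neither component measured, and the Protocol states no rule for that case. Secondly, the opportunity to detect an eGFR event differs by arm, because JADE visits may bring renal tests between CAs that the Protocol does not provide in DIAMOND. The endpoint as written asks for no confirmatory value, so each additional test is another chance to cross the threshold. More detection in JADE would make JADE look worse than it is. Equal under-recording would lower event rates and cost some power.

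**Working it through.** **1. The plan's own figure.** High-risk scenario, 0.10 against 0.08 over 2 years, two-sided alpha 0.05, power 80%, 1:1. The two-proportion formula is n = [z₀.₉₇₅√(2p̄q̄) + z₀.₈₀√(p₁q₁+p₂q₂)]² / (p₁−p₂)².

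With p̄ = 0.09: (1.960×0.4047 + 0.842×0.4045)² / 0.02² = 3213 per group. The continuity correction (n/4)[1+√(1+4/(n|p₁−p₂|))]² gives 3313, exactly as stated. Without the correction, 3313 per group has 81.2% power. No stated figure is in dispute; this only anchors the illustration in step 4.

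**2. Route against definition.**

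| Component | Phone or interview can establish it? | Scheduled measurement, both arms |
|---|---|---|
| Death, admissions, procedures, amputation, cancer | Yes, with documents | Not needed |
| eGFR <60, or <15 | No | CA at baseline, months 12 and 24 |
| Corrected acuity 20/200 or worse | No | CA at baseline, months 12 and 24 |

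**3. Follow-up after the last scheduled measurement** (uniform recruitment assumed).

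- Close-out at 36 months, 8 months of recruitment: the gap is 12 months for the first patient and 36−8−24 = 4 for the last. Mean gap 8 of a mean 32 months, 25%.
- Close-out at 36 months, 6 months of recruitment: 12 down to 6 months. Mean 9 of 33, 27%.
- Total of 2.5 years, 6 months of recruitment: 6 down to 0 months. Mean 3 of 27, 11%.

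**4. Possible size.** Let f be the share of primary events that only a measurement can show, and u the share of those events missed in an arm, for instance because the patient is reached only by phone. If missed events are scored as non-events, recorded risk = true risk × (1 − f·u). The Protocol gives neither quantity. Assumed ranges: f = 20-60%, u = 10-20%. The upper u borrows the 20% attrition allowance, which is not the same thing as phone-only follow-up.

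*Equal in both arms, 3313 per group:* power falls from 81.2% to 80.3% (f=20%, u=10%), 77.6% (f=40%, u=20%) or 75.6% (f=60%, u=20%), a loss of about 1 to 6 points.

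*Unequal, u = 10% in JADE and 20% in DIAMOND:* ratio = (1−0.10f)/(1−0.20f).

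| f | Ratio, no true effect | Ratio, true 0.80 | Power |
|---|---|---|---|
| 20% | 0.98/0.96 = 1.02 | 0.817 | 71.9% |
| 40% | 0.96/0.92 = 1.04 | 0.835 | 60.5% |
| 60% | 0.94/0.88 = 1.07 | 0.855 | 47.7% |

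If u were larger in JADE, the direction would reverse.

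**The case against.** The strongest reply is that interview is not the only source. Everyone who attends has eGFR and acuity measured at months 12 and 24, and item 11 sits in that same CA section with coinciding time points. Enrolment (item 2) obtains consent to collect biochemical data at least yearly for 3 years, and an adjudication committee reviews supporting documents. All of this stands, and it confines the under-recording to patients without a CA. It does not make item 11 correct, and no eGFR or acuity test is scheduled after month 24.

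Several stronger readings are tempting but not supported:

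- *Phone-only patients are counted as event-free.* Data Analysis says who enters, not how an unmeasured component is scored. They could be censored, and a sensitivity analysis for defaulters is planned. Detailed handling may be left to the SAP.
- *All time after month 24 is unmeasured.* JADE visits may include renal tests and biochemical data may be collected in either arm. If neither arm were tested, that stretch would add no measured events to either side and would leave the 24-month estimate unchanged.
- *DIAMOND patients miss more CAs.* No section says so. Default prevention covers both groups, and all patients must be willing to return.
- *A large bias.* Assuming a 6% risk and phone-only shares of 15% and 25% gives 5.1% against 4.5%, a ratio of 1.13. That concerns the measured components alone. For the composite, (1−0.15f)/(1−0.25f) is 1.02-1.07 for f = 20-60%.

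It is also fair to object that censoring by component inside a first-event composite is awkward: each patient has one observation time, and missing a CA may itself be related to illness. That belongs in a sensitivity analysis, not in the main rule.

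**Conclusion.** The point holds in this form. The Protocol lets phone or interview serve for outcomes that only a measurement can establish, admits patients reached only by phone to the primary analysis, continues past month 24 without a scheduled eGFR or acuity test, and allows extra renal testing in one arm. Measured components may be under-recorded in patients without a CA, and eGFR events may be detected more often in JADE. The second would work against JADE.

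The size is not known from the document. Equal under-recording costs about 1 to 6 points of power. A 10% against 20% difference in missed measured events moves the composite ratio from 1.00 to 1.02-1.07, or from 0.80 to about 0.82-0.86. These results rest on the assumed f and u and on missed events being scored as non-events.

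**What to change.** 1. **Comprehensive assessment, item 11.** Limit phone or interview ascertainment to death, hospitalised events, procedures, amputation and cancer. Derive the eGFR and acuity components only from values measured at the month-12 and month-24 CA, in both arms. This corrects the stated route and takes JADE's between-visit renal tests out of endpoint detection.
2. **Data Analysis, main analysis.** Run the primary analysis to the month-24 CA, which matches the 2-year study assumed for the sample size. Report reportable clinical events to close-out as supplementary.
3. **Data Analysis, sensitivity.** Add an analysis in which patients without a CA measurement are not taken to be free of the measured components, for example restricted to CA attenders or using multiple imputation.

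Cost: changes of wording in two sections, with no new visit or test. The main analysis has slightly fewer events and less follow-up time, and eGFR values obtained outside the CAs no longer count towards the endpoint.

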### Intervention – JADE Group

In the JADE group, the patients are managed by a team of doctor, nurse and HCA, who share different tasks ranging from clinical diagnosis, education, data management and treatment to targets in order to improve the logistics in delivering this complex care protocol, augmented by information technology.

[figure not shown]

- 1) Patients randomized to the JADE group will be followed according to the protocol based on their risk levels. In addition to the CA visit, all subsequent FU visits will be documented followed by data entry into the JADE portal with issue of reports to both patients and doctor to promote sharing of information and informed decisions.

| Risk stratification                           | Very-high risk
4                                                 | High risk
3 | Medium risk
2 | Low risk
1 |
|-----------------------------------------------|---------------------------------------------------------------------|----------------|------------------|---------------|
| Cardiovascular renal complication             | ≥ 1                                                                 | 0              | 0                | 0             |
| Any risk score                                | NA                                                                  | ≥ SP           | ≥ ST and < SP    | < ST          |
| Stratification parameters                     | NA                                                                  | ≥ 3            | 2                | 0-1           |
| eGFR                                          | NA                                                                  | < 60           | 60-90            | ≥ 90          |
| Recommended number of medical visits per year | 6 or more                                                           | 4 or more      | 3 or more        | At least 2    |
| Comprehensive assessment                      | Every 12-18 months                                                  |                |                  |               |
| Other recommendations                         | Counselling/laboratory tests/telephone calls between medical visits |                |                  |               |

Parameters for risk stratification:

1 Cardiovascular-renal complications: cardiovascular diseases (stroke, coronary heart disease and/or peripheral vascular disease with or without interventions or medications), heart failure and end-stage renal diseases [on renal replacement therapy or estimated glomerular filtration rate (eGFR) < 15 ml/min 1.73/m^2].

2 Risk score: high sensitivity (ST) and specificity (SP) cut-off points, derived from each of the four risk equations of the Hong Kong Diabetes Registry, were used to estimate probability of risk of clinical outcomes.

3 Stratification parameters: Current or ex-smoker; body mass index ≥ 27.5 kg/m^2 or waist circumference ≥ 80 cm in women or ≥ 90 cm in men; blood pressure > 130/80 mmHg or treatment with antihypertensive drugs; low-density lipoprotein-cholesterol (LDL-C) > 2.5 mmol/l; triglyceride (TG) ≥ 2.3 mmol/l and/or high-density lipoprotein-cholesterol (HDL-C) < 1.0 mmol/l; treatment with lipid-regulating drugs if LDL-C ≤ 2.5 mmol/l and TG < 2.3 mmol/l and HDL-C ≥ 1.0 mmol/l; random spot urinary albumin-creatinine ratio > 3.5 mg/mmol in women or > 2.5 mg/mmol in men; foot at risk defined by two of three of the following: sensory neuropathy, skin changes (e.g. fungal infection, dry skin) or deformities (e.g. claw feet or hallux deformities); retinopathy; HbA1c ≥ 8%.

4 eGFR in ml/min 1.73/m^2.

Risk levels:

1 Level 4: Presence of any cardiovascular or renal complication.

2 Level 3: No cardiovascular or renal complication; and either having three or more stratification parameters, or risk scores above the high specificity cut-off in any one of the risk equations, or eGFR < 60 ml/min 1.73/m^2.

3 Level 2: No cardiovascular or renal complication; none of the conditions (risk score, stratification parameters, eGFR) defined in the 'High risk' category but not belonging to the 'Low risk' category.

4 Level 1: No cardiovascular or renal complication; and having other condition fulfilling the 'Low risk' (one or less stratification parameter, and risk scores below the high sensitivity cut-off in all of the risk equations, and eGFR ≥ 90 ml/min 1.73/m^2).

- 2) After the patient has undergone CA, the nurse will arrange 2-4 hours of diabetes education in groups or individually and explain the various features of the JADE report.

[figure not shown]

- 3) If not yet put in place, the nurse/HCA will prepare a clinic folder for each patient and create a system to facilitate appointment booking and tracking of default.
- 4) Patients are booked for reviews led by the doctor-nurse-HCA team every 2-4 months, preferably in a setting different from the busy clinics in order to facilitate group education and promote peer support.
- 5) Between each FU visit, the nurse or HCA will contact the patient by phone or email to remind them of the appointments (e.g. medical FU visit or laboratory tests), adhere to medications and healthy lifestyles, perform self glucose monitoring and provide psychosocial support, as appropriate.
- 6) Before each FU visit, the nurse will ensure all tests (e.g. HbA1c, lipids, blood haemoglobin, renal function etc) ordered by the doctor are available in the folder for decision making.
- 7) At each FU visit, the patients will first see the nurse for record of BP, body weight and blood glucose (or HbA1c) as appropriate and enter them in the CRF. Patient's compliance will also be checked at each visit.
- 8) After the FU visit, the patients will see the nurse to clarify any issues and concerns. The nurse will reinforce compliance and record any changes in medications and note any procedures or tests ordered by the doctor. As and when appropriate, the nurse will remind doctors on action items prompted by the JADE e-portal, if omitted.
- 9) After each FU visit, the nurse will issue summary reports to be given to patients and doctors to promote sharing of information.

10) The FU and CA reports can be given to the patient on the same day of the visit or emailed or sent by post to patient as appropriate.

